### Group size calculation

Group size calculation is based on the number of appendices and gallbladders with a tumour with clinical consequences benefitting the patient that would have been missed in case of a selective policy. According to systematic reviews, the incidences of appendiceal neoplasms and GBC are 7 per 1000 and 4 per 1000 patients, respectively.^1 2^ Data regarding the ability of surgeons to recognise these abnormalities and the consequences of these neoplasms are insufficient. It is however estimated that less than 1 out of 1000 examined specimens will contain an appendiceal neoplasm or GBC with clinical consequences benefitting the patient that is not recognised by the surgeon during the macroscopic assessment. Selective HPE will be considered safe if this number does not increase to 3 per 1000 patients. To demonstrate non-inferiority of selective compared with routine HPE, a sample size of 4462 per cohort achieves a 84% power to detect a difference of 0.002 using a one-sided binomial test at a target significance level of 0.025, assuming a baseline and actual proportion of 0.001, and a non-inferiority limit of 0.00299. The actual significance level achieved by the Fisher's exact test is 0.021. These two cohorts (one for appendices, one for gallbladders) only include the specimens that would not have been sent for HPE in case of a selective policy. If the rate of HPE can be reduced to 20%, 5578 patients per cohort (4462/0.8) should initially be included.

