##### Costs

###### Economic evaluation

Considering that—under the non-inferiority hypothesis—1 or 2 per 1000 patients at maximum will experience health consequences from routine HPE, and 3 to 4 per 1000 patients may experience transient harm following unnecessary additional treatment, differences in effectiveness between the routine and selective strategy can best be addressed qualitatively (eg, by case reports). Quantitatively, a cost analysis from a healthcare provider will be the main focus of research.

During the study, all specimens will be sent for HPE, so the selective policy will not be observed. The comparison between both strategies will therefore be done through decision tree analysis. Observed distributions of histopathological findings under the routine policy will be used to define chance nodes in the reference tree of the model. Alternatively, both the distribution of histopathological findings in specimens that would have been sent for HPE as the distribution of histopathological findings in specimens that would not have been sent for HPE in case of a selective policy will be used to define chance nodes in the other main model tree.

In addition to the initial HPE, costs of other resources (eg, additional treatment, additional HPE, hospital stay) will be assigned to each end node in the model. If costs were observed under routine examination, but the specimen would not have been sent for HPE in case of a selective policy, they will be ignored if related to unnecessary use of healthcare resources. However, if these costs were justified, and the specimen would not have been sent for HPE in case of a selective policy, it will be assumed that these costs would nevertheless be generated at a later stage during the disease course, and thus included in the decision tree. In addition, a scenario analysis will be run with a 50% surplus penalty of these costs to compensate for yet unobserved extra costs of delayed healthcare at a later disease stage. Unit costing of hospital resources will be based on the Erasmus University Rotterdam/National Healthcare Institute guideline for costing in healthcare research.^26^ If specific unit costs are lacking in the guideline, local bottom-up or top-down costing initiatives in participating hospitals (eg, Amsterdam UMC) will be used.

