All probabilities at the chance nodes will be assumed beta-distributed. Multiple theoretical distributions will be assessed for fitting the (observed) distributions of healthcare costs at the end nodes of the decision tree. If theoretical fits seem insufficient, a uniform distribution will be defined for the (observed) cost data. Monte Carlo simulation will be applied based on 25 000 draws from each distribution of input parameters. It is expected that a time horizon for the cost analysis of 6 months is sufficient to reliably estimate the cost difference between routine and selective HPE. Separate models will be built for the analyses of appendices and gallbladders.

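### The cost simulation draws from the spread of observed patient costs rather than the uncertainty of the mean cost, and its uniform fallback can shift the mean when costs are skewed

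*Protocol article*

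**What the plan says.** The comparison of routine and selective examination is made by a decision tree (Economic evaluation). Besides the initial examination, "costs of other resources (eg, additional treatment, additional HPE, hospital stay) will be assigned to each end node in the model". The article then fixes how uncertainty is simulated:

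- Probabilities: "All probabilities at the chance nodes will be assumed beta-distributed".
- Costs: "Multiple theoretical distributions will be assessed for fitting the (observed) distributions of healthcare costs at the end nodes of the decision tree".
- Fallback for costs: "If theoretical fits seem insufficient, a uniform distribution will be defined for the (observed) cost data".
- Simulation: 25 000 "draws from each distribution of input parameters".

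It gives no bounds for the uniform distribution and no criterion for an insufficient fit. On costs seen under routine examination in specimens that the surgeon would not have sent, it says that "they will be ignored if related to unnecessary use of healthcare resources". Justified costs in such specimens are kept in the selective tree as well.

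**The concern.** Two things look wrong, and they are separate.

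First, the quantity simulated. A decision tree compares expected costs, so the uncertain parameter at an end node is the mean cost there. The distribution of observed costs describes how patients differ from each other, and that spread does not shrink as more patients are costed. The probabilities do receive a distribution for parameter uncertainty (the beta), so the model would mix two kinds of variation in one interval.

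Second, the fallback. A continuous uniform from the lowest to the highest observed cost has its mean at the midrange, which in skewed data is set largely by the single most expensive patient.

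The cost analysis is listed among the primary outcomes, and the abstract names cost savings as one of the two main outcomes. An interval that is too wide makes the saving look less certain than the data show. An inflated mean for treatment that the selective policy would avoid overstates the saving and favours that policy.

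**Working it through.** The cost section states no figure that could be reproduced.

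**Inputs from the article**
- Incidence (Group size calculation): "the incidences of appendiceal neoplasms and GBC are 7 per 1000 and 4 per 1000 patients, respectively".
- Inclusion: 5578 per cohort planned (4462/0.8 = 5577.5, which agrees); 6902 appendices and 8387 gallbladders at submission (Current status of the study).
- Unnecessary treatment (Economic evaluation): "3 to 4 per 1000 patients may experience transient harm following unnecessary additional treatment".

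**Assumptions, because the article gives no cost data:** right-skewed lognormal costs, coefficient of variation (CV) 0.6 to 1.0, 5 to 30 costed patients per node, and uniform bounds at the observed minimum and maximum.

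**Step 1: how many patients are costed**
- Neoplasms at planned size: 5578 × 0.007 = 39 appendiceal; 5578 × 0.004 = 22 gallbladder cancers.
- Neoplasms at the numbers included: 6902 × 0.007 = 48; 8387 × 0.004 = 34.
- Unnecessary treatment at planned size: 5578 × 0.003 = 17 to 5578 × 0.004 = 22 per cohort.

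These totals are divided over several end nodes, so 5 to 30 per node is a reasonable range.

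**Step 2: individual costs against the mean**

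The SD of a single drawn cost is s. The standard error of the mean is s/√n. Their ratio is √n, whatever the shape of the costs: √10 = 3.2 and √30 = 5.5.

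Example with a lognormal of mean 1, CV 1 and n=30. Here σ² = ln 2 = 0.693 and σ = 0.833. The central 95% range of individual costs runs from exp(−0.347 − 1.632) = 0.14 to exp(−0.347 + 1.632) = 3.62, a width of 3.5 times the mean. The interval for the mean has width 2 × 1.96 × 1/√30 = 0.72. The ratio is 4.9, a little below 5.5 because the range of individual costs is asymmetric. The fitted mean itself is not biased.

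**Step 3: the uniform fallback**

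Uniform mean = (min + max)/2; uniform SD = (max − min)/√12. Averages over 20 000 simulated samples per setting, given as CV 0.6 / CV 1.0:

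| n | uniform mean ÷ sample mean | uniform SD ÷ patient SD | uniform SD ÷ standard error |
|---|---|---|---|
| 5 | 1.11 / 1.22 | 0.7 / 0.7 | 1.6 / 1.6 |
| 10 | 1.24 / 1.50 | 0.9 / 0.9 | 2.9 / 2.8 |
| 20 | 1.41 / 1.89 | 1.1 / 1.1 | 4.9 / 5.0 |
| 30 | 1.52 / 2.14 | 1.2 / 1.25 | 6.7 / 6.8 |

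The first ratio grows with n, so more data make the bias worse. Gamma costs with CV 1 give 1.51 at n=10 and 2.01 at n=30, close to the lognormal. Symmetric (normal) costs give 1.00. Left-skewed costs (beta 5, 1.5) give 0.94 at n=10 and 0.89 at n=30.

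**Step 4: route into the saving**

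Let C be the mean cost of unnecessary treatment. If none of these specimens would have been sent, it contributes 0.003C to 0.004C per specimen to the saving. An inflation of 1.2 to 1.5 (n=10) turns this into 0.0036C (0.003 × 1.2) to 0.006C (0.004 × 1.5). An inflation of 1.5 to 2.1 (n=30) gives 0.0045C (0.003 × 1.5) to 0.0084C (0.004 × 2.1). Specimens that the surgeon would have sent anyway reduce this. Neither C nor the cost of an examination is in the article, so the share of the total saving cannot be worked out.

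**The case against.** **The fallback may seldom be used.** It applies only after several theoretical distributions have been tried. The lognormal costs simulated here would be fitted by a lognormal candidate: a Shapiro–Wilk test on the log costs rejects in about 5% of samples at n from 5 to 80, which is its nominal error rate. This stands. The simulation shows what the uniform does if it is used, not how often. A reader might infer that small, skewed nodes are just where parametric fits fail; nothing in the article supports that, and small samples rarely reveal misfit.

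**The bounds are not stated.** The fallback could also mean equal weight on each observed cost, which leaves the mean unbiased. This stands too, and it makes the bias conditional. The interval problem remains under that reading.

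**Most costs cancel.** Justified costs stay in both trees, so bias in their mean largely drops out of the main comparison. That is correct. It does not drop out of the scenario with a 50% surplus on those costs, where it would count against the selective policy.

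**The interval decides nothing.** No test or threshold is attached to the cost interval, and the term input parameters together with the beta distributions suggests that parameter uncertainty was intended. That is fair and lowers the stakes. Even so, the text names the observed costs as what is fitted, and an analyst who follows it would simulate the wrong quantity for a main outcome.

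**Conclusion.** The point holds in a limited form.

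- **Interval.** On the literal text, the cost component is about √n times too wide for a mean cost: about 3 times at n=10 and 5.5 times at n=30. This needs no assumption about skew or bounds. It does not bias the mean where a theoretical distribution fits.
- **Mean under the fallback.** It is inflated about 1.1 to 1.2 times at n=5, 1.2 to 1.5 times at n=10 and 1.5 to 2.1 times at n=30. This holds only with minimum-to-maximum bounds and right-skewed costs (assumed lognormal, CV 0.6 to 1.0).
- **Spread under the fallback.** The uniform is too wide against the standard error at every n examined. It exceeds the spread between patients only at the larger nodes (0.9 times at n=10, 1.1 times at n=20).

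Two stronger readings are tempting. One is that the mean could be inflated nearly threefold, and the spread about 14-fold relative to the standard error. Such figures need about 80 costed patients at one node, while the stated incidences imply only 22 to 48 neoplasms in a whole cohort. The other is that the reported saving is materially biased. The article gives neither treatment nor examination costs, so this cannot be shown. The primary safety outcome is unaffected.

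**What to change.** Replace the fallback sentence with: *If no theoretical distribution fits, the mean cost at the end node will be drawn by non-parametric bootstrap of the observed patient costs.* Where a theoretical distribution is used, state that the mean cost is drawn, for example from a gamma distribution set by the observed mean and its standard error, and not the cost of a single patient.

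This settles both the interval and the open question of bounds. It takes one or two sentences and a little code, with no new data. The small downside is that a bootstrap is itself unstable at nodes with very few patients, so the number of costed patients per node should be reported beside the result.

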###### Budget impact analysis

The budget impact analysis of selective HPE will be performed from governmental, insurance and hospital provider perspectives for a 4-year budget period, starting with the first full budget year after completion of the trial. The budget impact will be expressed in millions of euros. Primarily, the budget for care by medical specialists (code 0303), such as pathologists and surgeons, will be affected. For all perspectives, the reimbursement guidelines from the Dutch Healthcare Authority will be applied to the estimate actual expenses.

In case of negotiable reimbursement levels, the 10% trimmed mean purchase price per unit as provided by www.opendisdata.nl (eg, DBC code 119599010) will be used. Data on the incidences of performed appendicectomies and cholecystectomies will be gathered from public data sources (www.opendisdata.nl; www.statline.cbs.nl), and linearly extrapolated to forecast the numbers during the period for budget impact analysis.

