##### Cost analysis

The economic evaluation will be performed as a cost-minimisation analysis. In addition, a budget impact analysis of selective HPE will be performed from governmental, insurer and hospital provider perspectives.

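### The budget impact analysis prices the hospital perspective with the payers' reimbursement levels, so the hospital's own budget effect is not measured and could have the wrong size or sign

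*Protocol article*

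**What the plan says.** Cost analysis, under Primary outcomes, announces a cost-minimisation analysis and adds that "a budget impact analysis of selective HPE will be performed from governmental, insurer and hospital provider perspectives". The Budget impact analysis section sets its inputs:

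- **Perspectives and horizon:** the analysis "will be performed from governmental, insurance and hospital provider perspectives for a 4-year budget period".
- **Price:** "For all perspectives, the reimbursement guidelines from the Dutch Healthcare Authority will be applied to the estimate actual expenses".
- **Fallback price:** "In case of negotiable reimbursement levels, the 10% trimmed mean purchase price per unit as provided by" a public website is used, with no split by perspective.
- **Volume:** national counts from public sources, "linearly extrapolated to forecast the numbers during the period for budget impact analysis".
- **Budget concerned:** "Primarily, the budget for care by medical specialists (code 0303), such as pathologists and surgeons, will be affected".

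The Economic evaluation section, which describes the separate decision-tree analysis, has a different price basis: "Unit costing of hospital resources will be based on the Erasmus University Rotterdam/National Healthcare Institute guideline for costing in healthcare research", with local costing in participating hospitals where the guideline has no figure. The budget impact section does not refer to these unit costs.

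**The concern.** The purpose of three perspectives is that one change in practice affects each party's budget differently. The payer stops paying for an examination. The hospital stops incurring its cost and may also stop receiving the payment. A tariff or purchase price measures the payer's side of this. Used as the hospital's expense, it measures neither the cost avoided nor the income forgone.

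Potential cost savings are one of the study's two main outcomes, and the article expects guidelines to be adjusted to the results. A hospital reading the provider perspective would take it as the effect on its own budget. Under this rule it would be reading a payer's figure, which could show a saving where the hospital makes a loss.

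**Working it through.** The article states no budget impact result, tariff or unit cost, so there is no figure to reproduce. The check compares what the stated rule yields with what the hospital's budget would show.

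**Inputs from the article**
- Annual procedures (Introduction): 16 000 + 22 500 = 38 500.
- Examination rate under a selective policy (Group size calculation): 20%, a conditional planning assumption and not a result.
- Examinations avoided a year: n = 38 500 × 0.80 = 30 800. This takes all specimens as currently examined.

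**Assumed inputs, not in the article**
- Tariff per examination, T: EUR 100, with a range of EUR 50 to 150.
- Hospital cost avoided per examination, C: 0.25 to 1.25 times T.

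**Formulas**
- The plan's pricing, any perspective: n × T.
- Hospital's own effect: n × (C − L), where L is the payment lost per examination.
- Paid per examination: L = T, giving n × (C − T).
- Bundled or fixed payment: L = 0, giving n × C.

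The plan's figure equals the hospital's effect when C − L = T. If no payment is lost, that requires avoided cost equal to the tariff. If payment is lost, avoided cost would have to exceed the tariff by exactly the amount lost, which would be a coincidence.

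**Results at T = EUR 100, in EUR million a year (positive = saving)**

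| C/T | Plan's pricing | Hospital, paid per examination | Hospital, bundled |
|---|---|---|---|
| 0.25 | 3.08 | −2.31 | 0.77 |
| 0.50 | 3.08 | −1.54 | 1.54 |
| 1.00 | 3.08 | 0 | 3.08 |
| 1.25 | 3.08 | 0.77 | 3.85 |

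For example, at C/T = 0.50 with payment per examination: 30 800 × (50 − 100) = −1 540 000. Bundled: 30 800 × 50 = 1 540 000.

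The plan's figure is 30 800 × 50 = EUR 1.54 million at the lowest tariff and 30 800 × 150 = EUR 4.62 million at the highest. The hospital figures scale in proportion to T.

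The plan's figure matches the hospital's effect in one of the eight hospital cells: bundled payment with cost equal to tariff. Under bundled payment the insurer pays the same whether or not the specimen is examined, so n × T then overstates the insurer's saving unless the bundle price is renegotiated. Only the initial examination is priced here; later treatment and hospital stay are left out.

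**The case against.** Several points on the other side have force.

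- **The perspectives need not coincide.** A reader might infer that the three perspectives are bound to give the same answer. The article does not support that. It names no input that differs by perspective, but the services, budgets or payers counted in each could differ, and code 0303 is described only as the budget primarily affected.
- **Lost income need not be shown as a saving.** A reader might also infer that this will certainly happen. It requires payment that falls with each examination, and the article does not describe how hospitals are paid. It also gives no sign convention; reimbursement levels could be used in the hospital perspective to count forgone income. However, the sentence assigns them to expenses, and no revenue term is mentioned.
- **The key sentence is poorly worded.** It might mean that tariffs stand in for expenses or that they are applied to an estimate of them. On either reading, reimbursement prices are the basis for the hospital as well.
- **A provider-side result exists elsewhere.** The Economic evaluation says "Quantitatively, a cost analysis from a healthcare provider will be the main focus of research", and it uses hospital unit costs. That limits the damage but does not repair this analysis: it has a 6-month horizon, no reimbursement term and no national 4-year budget.
- **An article leaves detail to a fuller plan.** Scope and bundling status could well be found there. The price basis is different, because the article states it as a rule for all perspectives, and a fuller plan that followed the rule would carry the same problem.
- **The amounts depend on assumptions.** This is correct. In particular, the sign under payment per examination turns positive once avoidable cost exceeds the tariff.

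**Conclusion.** The point holds for the hospital provider perspective of the budget impact analysis. One reimbursement-based price, one fallback price and one volume forecast serve all three perspectives, and no hospital cost or revenue term is given. The hospital's own budget effect is therefore not separately measured, and the reported figure can be wrong in size under either payment system and wrong in sign if payment falls with each examination avoided.

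The size cannot be established from the article. The count of 30 800 rests on the 20% planning assumption, and tariffs and avoidable costs are assumed throughout, so the euro amounts show only the direction and form of the error.

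It would go too far to conclude that the cost outcome as a whole is invalid. The decision-tree cost analysis, which the article treats as its main focus, has its own unit costs and is not affected. Neither is the oncological safety outcome.

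**What to change.** In Budget impact analysis, restrict the reimbursement-price sentence, and the trimmed mean purchase price that follows it, to the governmental and insurer perspectives. Then add a rule for the hospital, for instance:

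> For the hospital provider perspective, the budget impact is the change in the hospital's own resource cost, valued with the unit costs of the economic evaluation, net of any change in reimbursement received.

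State whether histopathological examination is paid separately or within a bundled product, since this decides both the hospital's revenue term and whether the insurer saves anything. State which services and budgets each perspective counts, and report the three results side by side.

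The cost is one paragraph of wording and a small extra calculation. The hospital unit costs are already planned and no further patient data are needed, but the payment arrangement has to be established. The hospital figure may turn out less favourable than the payer-priced one.

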#### Secondary outcomes

All incidences of histopathological diagnoses will be reported in absolute numbers and percentages. The incidence of different histopathological diagnoses will be presented as shown in table 4 (appendices) and table 5 (gallbladders). These tables will also provide information on which specimens would and would not have been sent for HPE in case of a selective policy. Table 6 will show whether or not specimens containing an appendiceal neoplasm or GBC were reported as suspicious by the surgeon and whether or not the surgeon believed HPE was indicated. Details on all patients with an appendiceal neoplasm or GBC will be presented as proposed in table 7 (appendices) and table 8 (gallbladders).

**Table 4 T4:** Histopathological diagnoses after appendicectomy for appendicitis

			Total (n=)	Indication for HPE^a^ (n=)	No indication for HPE^a^ (n=)
Histopathological diagnosis		Normal appendix	n (% of ‘Total’)	n	n
		Acute inflammation	n (% of ‘Total’)	n^b^	n^c^
		Chronic inflammation and reactive changes	n (% of ‘Total’)	n	n
	Appendiceal neoplasms	Neuro-endocrine neoplasm	n (% of ‘Total’)	n	n
		Non-invasive epithelial neoplasm	n (% of ‘Total’)	n	n
		Invasive epithelial neoplasm	n (% of ‘Total’)	n	n
		Lymphoma	n (% of ‘Total’)	n	n
	Non-neoplastic aberrant findings	Parasitic infection	n (% of ‘Total’)	n	n
		Endometriosis	n (% of ‘Total’)	n	n
		Granulomatous disease	n (% of ‘Total’)	n	n
		Other	n (% of ‘Total’)	n	n

a. According to the operating surgeon or surgical resident.

b. Uncomplicated acute appendicitis (n=), complicated acute appendicitis (n=); as reported in pathology report.

c. Uncomplicated acute appendicitis (n=), complicated acute appendicitis (n=); as reported in pathology report.

HPE, histopathological examination.

**Table 5 T5:** Histopathological diagnoses after cholecystectomy for presumed benign gallbladder diseases

			Total (n=)	Indication for HPE^a^ (n=)	No indication for HPE^a^ (n=)
Histopathological diagnosis		Normal gallbladder	n (% of ‘Total’)	n	n
		Acute inflammation	n (% of ‘Total’)	n	n
		Chronic inflammation and reactive changes	n (% of ‘Total’)	n	n
	Gallbladder neoplasms	Adenoma	n (% of ‘Total’)	n	n
		Biliary intraepithelial neoplasm	n (% of ‘Total’)	n	n
		Carcinoma	n (% of ‘Total’)	n	n
		Other malignant neoplasms	n (% of ‘Total’)	n^b^	n^c^
	Non-neoplastic aberrant findings	Cholesterol polyp	n (% of ‘Total’)	n	n
		Inflammatory/hyperplastic polyp	n (% of ‘Total’)	n	n
		Adenomyomatosis	n (% of ‘Total’)	n	n
		Other	n (% of ‘Total’)	n	n

a. According to the operating surgeon or surgical resident.

b. Details on histology.

c. Details on histology.

HPE, histopathological examination.

**Table 6 T6:** Value of the intraoperative assessment by the surgeon for detection of appendiceal neoplasms/GBC

	Appendiceal neoplasm/GBC (n=)	No appendiceal neoplasm/GBC (n=)	Total (n=)
**Presence of abnormalities suspicious for malignancy**	n (% of ‘Appendiceal neoplasm/GBC’)	n (% of ‘No appendiceal neoplasm/GBC’)	n (% of ‘Total’)
**Indication for HPE**	n (% of ‘Appendiceal neoplasm/GBC’)	n (% of ‘No appendiceal neoplasm/GBC’)	n (% of ‘Total’)

GBC, gallbladder cancer; HPE, histopathological examination.

**Table 7 T7:** Details of patients with a histopathological diagnosis of an appendiceal neoplasm

Case	Sex, Age	Preoperative imaging	Assessor	Macroscopic abnormalities suspicious for neoplasm	Indication for HPE according to surgeon	Histopathological diagnosis	Additional diagnostic and/or therapeutic procedures	Remaining tumour tissue	Positive lymph nodes	90-day complications
**1**										
**2**										
**3**										
**…**										

HPE, histopathological examination.

**Table 8 T8:** Details of patients with a histopathological diagnosis of GBC

Case	Sex, Age	Preoperative imaging	Preoperative diagnosis	Surgical setting	Assessor	Macroscopic abnormalities suspicious for neoplasm	Indication for HPE according to surgeon	Histopathological diagnosis	Additional diagnostic and/or therapeutic procedures	Residual disease	90-day complications
**1**											
**2**											
**3**											
**…**											

GBC, gallbladder cancer; HPE, histopathological examination.

Several exploratory subgroup analyses will be performed. For appendiceal specimens, the influence of age (adults vs children) on the incidence of different histopathological diagnoses will be evaluated and reported in a similar way as shown in table 4. For gallbladder specimens, a subgroup analysis on the influence of preoperative diagnosis (cholecystitis vs gallstone disease) on the incidence of different histopathological diagnoses will be performed. Furthermore, the influence of the assessor (surgeon vs resident) and hospital (academic hospital vs teaching hospital vs non-teaching hospital) on the rate of specimens that would have been sent for HPE will be reported.

